**Level of Project**

| Faculty Research |
| --- |
| Post-Doctoral Research X |
| Student Research: Doctoral  Masters  Student Number |

**5. OTHER RESEARCH ETHICS BOARD APPROVAL(S)**

(a) Does the research involve another institution or site? Yes X No

(b) Has any other REB approved this project? Yes X No

If **Yes** please provide a copy of the approval letter upon submission of this application.

If **No**, will any other REB be asked for approval?

Yes        (please specify which REB) No

**6. FUNDING OF THE PROJECT**

(a) Please check one:

| Funded | Agency: Canadian Institutes of Health Research | Fund #: **245899** |
| --- | --- | --- |
|  | Agency: Canada Research Chairs Program (Salary support for [name]) | Fund #: N/A |
| Applied for funding | Agency: | Submission date: |
|  | Agency: | Submission date: |
| Unfunded | | |

**If one protocol is to cover more than one grant, please include all fund numbers.**

(b) If waiting for funding, do you wish to postdate ethics approval to the release of funds?

Yes  No

(c) For funded research, will more than one protocol be submitted to cover all research funded by the respective grant? Yes  No X

If **Yes**, this is #

**7. CONTRACTS**

Is there a funding or non-funded agreement associated with the research?

Yes  No

If **Yes**, please include 3 copies upon submission of this application. The contract between Pearson/Cogmed and University of Toronto is in process.

**8. PROJECT START AND END DATES**

Estimated start date for this project: Jan 2012 (for the start of amended protocol)

Estimated completion date for this project: August 2014

**9. SCHOLARLY REVIEW**

Please check one:

The research has been approved by a thesis committee, or equivalent (required for thesis research)

X The research has undergone scholarly review prior to this submission for ethical review

**Scientific peer review by CIHR**

The research will undergo scholarly review prior to funding

      (specify review committee)

The research will not undergo scholarly review apart from this ethics review

**10. CONFLICTS OF INTEREST**

(a) Will the researcher(s), members of the research team, and/or their partners or immediate family members:

(i) Receive any personal benefits (e.g. financial benefit such as remuneration, intellectual property rights, rights of employment, consultancies, board membership, share ownership, stock options, etc.) as a result of or in connection to this study? Yes  No

(ii) If **Yes**, please describe the benefits below. (Do not include conference and travel expense coverage, or other benefits which are standard to the conduct of research.)

NO, except that Cogmed-Pearson provide the research software licences without cost for this research study

(b) Describe any restrictions regarding access to or disclosure of information (during or at the end of the study) that has been placed on the investigator(s). This includes controls placed by sponsor, advisory or steering committee.

None

(c) Where relevant, please explain any pre-existing relationship between the researcher(s) and the researched (e.g. instructor-student; manager-employee; minister-congregant).

N/A

| **SECTION B – SUMMARY OF THE PROPOSED RESEARCH** |
| --- |

**Please include a list of appendices for all additional materials submitted.**

**11. RATIONALE**

Attention-Deficit/Hyperactivity Disorder (ADHD) and Learning Disability (LD) are among the most common neurobehavioural disorders, with prevalence rates estimated at about 5% to 9% ([1](#_ENREF_1), [2](#_ENREF_2)). Approximately 4% of youth in the United States have a comorbid diagnosis of ADHD and a Learning Disability (ADHD/LD) ([3](#_ENREF_3)). Research has shown ADHD/LD symptoms persist into young adulthood, a time when many are enrolled in post-secondary education. Students with ADHD/LD at the post-secondary education level constitute an emergent subgroup of the ADHD and LD populations that have received far less attention in the literature compared to children, adolescents and employed adults. The actual percentage of college students with ADHD/LD is unknown; however, some estimates suggest that 2-8% of students attending post secondary education have ADHD, LD or both (3). Youth with the additive problems of both disorders are at high risk for academic failure, and poor psychosocial and occupational outcomes in adulthood ([3](#_ENREF_3)). The “multiple deficit model” suggests that there is a common genetic and neuropsychological underpinning to these disorders ([3](#_ENREF_3)). For example, ADHD and LD share similar features, such as core deficits in processing speed and working memory ([4](#_ENREF_4), [5](#_ENREF_5)). ADHD and LD are each associated with several cognitive difficulties including poor working memory (WM) and processing speed ([4](#_ENREF_4), [5](#_ENREF_5)). WM is a “mental workspace” that provides temporary storage and manipulation of information and is closely related to *g*, a proposed measure of general cognitive ability ([6](#_ENREF_6)). In addition, WM has also been found to predict academic achievement ([7-9](#_ENREF_7)). One major problem is that current intervention approaches for ADHD/LD do not target the underlying cognitive deficits fundamental to these diagnoses. Thus, interventions that address underlying cognitive difficulties, such as WM, are a promising avenue of additional treatment for youth with combined ADHD/LD.

WM capacity has generally been thought to be a fixed trait, but recent studies have suggested that it can be improved by intensive and adaptive computerized training ([10](#_ENREF_10)). This intervention approach has been evaluated in children and adolescents with ADHD, older adults, and adult stroke patients and shown promising results ([11-14](#_ENREF_11)). Subjects not only improved on the trained WM tasks, but some of the studies suggest that improvements may generalize to non-trained WM activities, complex reasoning tasks, academic functioning, and behavioral symptoms of ADHD or working memory failure ([11](#_ENREF_11), [15](#_ENREF_15)). Moreover, brain imaging studies have provided converging evidence of training-related improvements in working memory: specifically increased activation has been found in cortical regions implicated in working memory ([14](#_ENREF_14), [16](#_ENREF_16), [17](#_ENREF_17)). However, no studies to date have investigated whether WM capacity can be improved in a population of young adults with ADHD/LD enrolled in post-secondary education programs. Nor have the results been replicated or elaborated upon using different imaging methodologies, like EEG (Electroencephalography), which is able to capture the millisecond time parameters of cognitive processing and so may provide new insights into the neural mechanism of WM and effects of WM training.

The overall objective of the current study is to determine the effectiveness of WM training, as administered by community-based psychologists licensed to provide this training, for college students with ADHD/LD. Specific objectives are to determine whether; i) high-intensity computerized WM training enhances WM capacity in college students with ADHD/LD, using behavioural as well as neuroimaging indices of change; ii) lower-intensity training would also result in improvements in WM; iii) WM training normalizes WM, as compared to typically developing peers (i.e., a healthy comparison group of college students); iv) improvements in WM will generalize to secondary outcome tasks, such as inhibitory control and planning; v) WM training will also ameliorate ADHD symptoms of inattention and hyperactivity; and vi) improvements will be sustained for at least a few months after completing the training.

**12. METHODS**

*Intervention*

The Cogmed Working Memory Training Program ([www.cogmed.com](http://www.cogmed.com)) will be used as the experimental program because of preliminary evidence indicating its effectiveness in enhancing WM ([10](#_ENREF_10), [11](#_ENREF_11), [13](#_ENREF_13), [14](#_ENREF_14)). Training is implemented with a software program “Cogmed QM” © from Pearson/Cogmed. It includes a set of auditory verbal and visual-spatial WM tasks presented via computer. All tasks involve: maintenance of simultaneous mental representations of multiple stimuli, unique sequencing of stimulus order in each trial and progressive adaptation of difficulty level as a function of individual performance.

There are a total of 13 different WM training exercises that include both auditory verbal and visual spatial modalities. Participants complete 8 of the 13 tasks every day, 15 trials of each task. An example of a visual spatial task is “3D grid”. In this task, there is a 3D box that is comprised of smaller boxes. The boxes light up in sequence and the participant must click on the boxes that lit up in the correct order. Task demands intensify as the number of boxes that light up increases. An example of an auditory verbal task is “Hidden”. In the task, a voice recites a series of numbers then a grid appears on the screen with numbers 1 through 9 and participants must click on those numbers they heard aloud, but in reverse order. Task demands intensify as the number of numbers increases.

The traditional training program is intensive, requiring approximately 30 min/day, 5 days a week for 5-6 weeks. Participants are required to complete 90 WM trials on each training day. Training plans are individualized and are modified according to performance, but the typical plan includes 13 tasks with 15 trials of 8 tasks each day. Responses are automatically logged to an electronic file, which is uploaded via the internet to servers at JVS to verify compliance.

*Study Design*

The study uses a randomized controlled design in which participants are randomly assigned to one of three groups: standard-length version of high-intensity WM training, a novel shorter version of the high-intensity WM training, or a wait-list control group. The standard-length WM training group will undergo 25 training sessions for 30 min/day, 5 days a week for 5 weeks and receive weekly phone calls from a cogmed coach to review progress and adjust the training as needed; the group assigned to the shorter version of the high-intensity training will also undergo 25 training sessions but for just 15 min/day, 5 days per week for 5 weeks and also receive the same type of weekly phone calls from a cogmed coach; and the wait-list group will not undergo any WM training during the 5 week period but will receive weekly phone calls from a member of the research team to review progress and advice on time management, organization, and mnemonic strategies. All groups will undergo pre testing, testing three weeks following completion of training and again at three-month follow-up. The wait-list group will be offered the cogmed training after the follow-up assessment. We will also recruit a group of healthy age- and gender-matched peers who will be assessed once and will not undergo WM training; this comparison group allows us to determine initial group differences in behavioral and neural indices of WM and whether WM training normalizes these indices in the ADHD groups.

*Diagnostic screening measures* (Baseline assessment only for AHD/LD and healthy controls).

All participants must have received a prior diagnosis of ADHD/LD to register with the college/university Student Disability Services. Since there is no standardized assessment used by Student Disability Services, we will administer a brief interview and standardized rating scales and screening tests to quantify the current symptoms of ADHD, and other clinical problems such as mood and stress levels.

*Adult ADHD Self-Report Scale* (ASRS v1.1) is a reliable and valid scale for evaluating ADHD in adults ([20](#_ENREF_20), [21](#_ENREF_21)). The ASRS v1.1 is an instrument consisting of eighteen questions based on the criteria used for diagnosing ADHD in adults using DSM-IV-TR criteria. Questions focus on how often ADHD symptoms occur (0=never, 1=rarely, 2=sometimes, 3=often, 4=very often). Scores for each item are added to calculate a total score.

*Kessler-10 (K10+).* The interviewer administered K10+ is a widely used psychological screening tool that aims to collect information on the individual’s current symptoms and to establish a productive dialogue. The 10-items yield a global measure of distress based on non-invasive questions about anxiety and depressive symptoms that an individual has experienced in the most recent 4-week period. Answers are multiple choice. <http://www.hcp.med.harvard.edu/ncs/ftpdir/k6/IWER%20K10.pdf>

*Symptom Assessment-45 (SA-45)* The SA–45 is a brief screen for various mental health symptoms, based on the well-validate longer version (SCL–90–R). It is often used as a screening tool, to help in diagnosis, to develop treatment plans, and to measure outcomes. Its items cover symptoms of obsessive compulsivity, psychoticism, somaticization, sensitivity to others, hostility to others, paranoid ideation, phobias, and depression. It is used in this study to allow us to describe the sample and to provide continuous measures of other types of psychopathology that might contribute to cognitive function

*Woodcock Johnson-III Tests of Achievement* ([18](#_ENREF_18)). Participants will complete three subtests: Math Fluency and Reading Fluency tasks determine automaticity of identifying words and recalling math facts; the Applied Problems subtest assesses mathematical reasoning ability. Scores below 16^th^ percentile will be used to support an LD diagnosis.

*Wechsler Abbreviated Scale of Intelligence (WASI).* This is a quick and reliable measure of intelligence ([19](#_ENREF_19)). The WASI consists of four subtests: Vocabulary, Similarities, Block Design, and Matrix Reasoning. In the interest of time, we will only administer the 2-subtests form, which will yield an estimate of general intellectual ability.

*Colour Perception Screening Tests*. Several of our key measures use coloured stimuli. Thus we will screen for color perception using two brief clinical measures: The *Farnsworth-Munsel 100 Hue Test* ([22](#_ENREF_22)) and the *Mollon-Refflin Minimalist Colour Vision Test (*[*23*](#_ENREF_23)*),* which screen for red-green and blue-yellow perception problems.

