**13. PARTICIPANTS OR DATA SUBJECTS**

The sample will include college students with ADHD and/or Learning Disabilities attending the University of Toronto, York University, Humber, Ryerson, or George Brown. The estimated sample size is 160 participants (40 in experimental, 40 in low intensity, 40 in waitlist, and 40 normal healthy controls). Participants will be of no relationship to the investigators. Those who participate in the study must be enrolled as full time students. All participants must have received a previous diagnosis of ADHD and/or a Learning Disability. Exclusionary criteria will include uncorrected sensory impairment, evidence of a neurological dysfunction or a history of psychosis. Personal information, and checks on eligibility, will be obtained directly from the participants during the intake procedures which are appended to this proposal. Ethics approval will be sought for institutions other than the University of Toronto in accordance with those institutions’ policies and procedures.

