**16. COMPENSATION**

(a) Will participants receive compensation for participation?

**Financial** Yes  No

In-kind Yes  No

Other Yes  No

(b) If **Yes**, please provide details.

Participants will receive $40 for the first visit, $80 for the second visit, and $80 for the last, follow-up visit. The comparison group will receive $60 for their visit.

(c) Where there is a withdrawal clause in the research procedure, if participants choose to withdraw, how will you deal with compensation?

Participants will be paid for their presence at the testing lab, even if they withdraw during that testing session.

| **SECTION C –DESCRIPTION OF THE RISKS AND BENEFITS OF THE PROPOSED RESEARCH** |
| --- |

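### Healthy peers are tested once, so comparing their score directly with trained participants' later scores mixes retest practice with the training effect and can look like normalisation

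*Protocol*

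**What the plan says.** Protocol Section 11 (Rationale) lists six specific objectives. The third is whether "WM training normalizes WM, as compared to typically developing peers".

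Protocol Section 12 (Methods, Study Design) sets the testing schedule for the two training arms and the wait-list: "All groups will undergo pre testing, testing three weeks following completion of training and again at three-month follow-up". The wait-list stays untrained throughout: "The wait-list group will be offered the cogmed training after the follow-up assessment". The healthy age- and gender-matched peers are described separately as a group "who will be assessed once and will not undergo WM training; this comparison group allows us to determine initial group differences". The same sentence gives that single assessment a second use, which is to show "whether WM training normalizes these indices in the ADHD groups".

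Section 16 (Compensation) agrees with this schedule. Randomised participants are paid for three visits, while "The comparison group will receive $60 for their visit". Section 13 plans 40 people in each of the four groups.

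The only analysis named in Section 12 is repeated measures ANOVA. The protocol mentions no practice or retest effects, no alternate test forms and no second peer assessment. It does not say how the normalisation question will be tested.

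**The concern.** The outcomes are mostly performance tasks: span tests, spatial working memory, planning, rapid naming, rule shifting and three EEG tasks. People can do better on such tasks simply because they have met them before. At post-test a trained participant is on a second exposure, and at follow-up on a third. The only peer score available is from a first exposure.

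If a trained participant's later score is set against that peer score, the remaining gap shrinks by the training effect plus the practice gain, and the peers had no chance to show a practice gain of their own. A programme with no effect could then appear to bring working memory, or brain activity, closer to the healthy level. At stake is the answer to objective iii.

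**Working it through.** **Inputs from the protocol.** Peers are assessed once and the randomised groups three times (Section 12, confirmed by the payments in Section 16). There are 40 people per group (Section 13; 4 × 40 = 160, which matches the stated total). The protocol gives no alpha, power, SD, baseline gap or practice gain, so it has no figure of its own on this point to reproduce.

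**Which comparisons are affected.**
- Peers v ADHD/LD at baseline: first exposure on both sides. Sound as regards practice.
- Training v wait-list at post-test or follow-up: same number of exposures in each arm, and randomised. Unaffected.
- Trained arm at post-test or follow-up v the single peer score: second or third exposure against first. Confounded.

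**Size, under stated assumptions.** Take SD = 1, a true training effect of zero, a baseline gap of 0.8 SD and practice gains of 0.2 to 0.4 SD.

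Share of the gap closed by practice alone = practice gain / baseline gap: 0.2/0.8 = 25%; 0.4/0.8 = 50%.

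Standard error of a 40 v 40 difference = √(2/40) = 0.224 SD. With 78 degrees of freedom the two-sided 5% critical value is 1.991, so the 95% confidence interval half-width is 1.991 × 0.224 = 0.445 SD.

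The chance of a non-significant difference from peers comes from the noncentral t distribution with noncentrality (remaining gap)/0.224:

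| Baseline gap (SD) | Practice gain (SD) | Remaining gap (SD) | Chance of non-significance |
| --- | --- | --- | --- |
| 0.8 | 0 | 0.8 | 5.8% |
| 0.8 | 0.2 | 0.6 | 24.5% |
| 0.8 | 0.3 | 0.5 | 40.2% |
| 0.8 | 0.4 | 0.4 | 57.6% |
| 0.5 | 0 | 0.5 | 40.2% |
| 0.5 | 0.2 | 0.3 | 73.7% |
| 0.5 | 0.3 | 0.2 | 85.7% |

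Two effects are at work and should be kept apart. Moving down within one baseline gap shows the effect of practice. The 0.5 SD row without practice shows that, at this sample size, a non-significant result is weak evidence of equality even with no retest problem.

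**What the available data can support.** Suppose peers, had they been retested, would have gained as much as the wait-list did. The residual deficit after training is then

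(peer baseline + wait-list change) − trained post-test.

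Randomisation makes the expected baselines of the trained and wait-list arms equal, so this becomes

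(peer baseline − ADHD/LD baseline) − (trained post-test − wait-list post-test).

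The first bracket compares first exposure with first exposure. The second is the randomised contrast. Practice cancels.

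**Precision of that estimate, approximately.** Pool the 120 randomised participants at baseline and treat the two brackets as uncorrelated, as they are after baseline adjustment. If adjustment gains nothing, the standard error is at most √(1/40 + 1/120 + 2/40) = 0.289 SD, a 95% half-width of 1.96 × 0.289 = 0.57 SD. If the training effect were known exactly, the floor would be 1.96 × √(1/40 + 1/120) = 0.36 SD. The true value lies between these.

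**The case against.** The strongest reply is that the protocol never writes down the faulty comparison. It says what the peer group makes it possible to determine, and it names only a basic analytic approach. Three stronger readings are tempting, and the text supports none of them.

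- A reader might infer that normalisation will be declared when p exceeds 0.05. No such rule appears. The contrast, margin and interval are commonly left to an SAP, which is not shown here.
- A reader might infer that the wait-list is left out of the normalisation question. The protocol is silent on this. It refers to the ADHD groups in the plural and retests the wait-list on the same schedule, so silence is not exclusion.
- A reader might infer that objective iii will be answered yes too often. That would follow only under a rule that looks at the trained arms alone. If training did nothing, the randomised contrast would tend to show no effect and the wait-list would drift towards the peers as well, which would expose the artefact.

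It is also fair to say that the size rests wholly on assumed values, and that objectives i and ii do not depend on the peer group.

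What remains is the design itself. The number of peer assessments is fixed in this protocol, and so is the use of that one assessment for normalisation. An SAP could choose a better contrast, but it could not supply peer retest data.

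**Conclusion.** The concern holds in a limited form. The single peer assessment is a proper comparator for the baseline gap. It is not one for trained scores at post-test or follow-up, where a direct comparison mixes practice with training and can look like normalisation even if training does nothing.

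With an assumed 0.8 SD gap, practice gains of 0.2 to 0.4 SD would close a quarter to a half of it and raise the chance of a non-significant difference from 6% to between about 25% and 58%. With an assumed 0.5 SD gap that chance is already 40% before any practice. The non-significance figures matter only if normalisation is judged by a significance test. The shrinkage of the observed gap does not depend on any test.

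This is a should-fix. It bears on one of six objectives, which uses a non-randomised comparator, and it leaves the randomised contrasts intact.

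**What to change.** In Section 12, Study Design, limit the direct peer comparison to baseline. Define normalisation through the residual deficit: the baseline gap (peers minus ADHD/LD, both at first exposure) minus the randomised, baseline-adjusted training-minus-wait-list difference. Compute it for each training arm, give a confidence interval (a bootstrap would do), and claim normalisation only if the interval excludes a deficit larger than a margin fixed beforehand. State the assumption that peers would gain from retesting about as much as the wait-list.

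The cost is a change of wording and analysis, with no new visits. There are two downsides. The wait-list receives weekly calls with advice on organisation and mnemonic strategies, so its change may not be pure retest gain. Subtracting it may understate the training effect and overstate the residual deficit. And with 40 per group and a half-width of roughly 0.36 to 0.57 SD, the result may be inconclusive.

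Retesting the peers on the same schedule without training would measure their practice gain directly and is the stronger repair, but it needs additional visits.
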